# Digital Assessment of Wellbeing in New Parents (DAWN-P): protocol of a randomised feasibility trial comparing digital screening for maternal postnatal depression with usual care screening

**DOI:** 10.1186/s40814-025-01631-7

**Published:** 2025-04-12

**Keywords:** Postnatal depression, Digital mental health, mHealth, Smartphone, Maternal mental health, Screening

## Abstract

**Background:**

Meta-analyses indicate that 17% of mothers experience postnatal depression (PND) in the year following childbirth, with suicide the leading cause of direct maternal death between 6 weeks and 12 months postpartum. The consequences and costs of PND are particularly high due to impacts on infants as well as parents. If detected, PND usually responds well to psychological treatment and/or medication but national reports indicate > 50% of cases are undetected. To improve detection, we developed a digital screening system (CareLoop PND) whereby mothers use an app to monitor their mood daily using a validated measure (Edinburgh Postnatal Depression Scale; EPDS), with real-time responses uploaded to a secure server. In this paper, we describe the protocol of a study to determine feasibility of delivering a full-scale RCT comparing digital screening with standard NHS practice.

**Methods:**

In this single-blind randomised feasibility trial, participants (*n* = 80) will be recruited during late pregnancy from two NHS maternity services and randomised (1:1) to receive CareLoop PND alongside their usual NHS care, or usual care alone. Those in the experimental arm will use the CareLoop PND app daily from ≥ 36 weeks’ pregnancy until 8 weeks postpartum. During this period, participants scoring above EPDS screening thresholds (via the app or standard care) will be assessed to confirm diagnosis. True positive PND cases identified by digital screening will be referred to services for support. A blinded researcher will conduct follow-up assessments using clinical and health economic measures at 8 weeks and 6 months postpartum. At 8 weeks postpartum, experimental arm participants will also provide qualitative and quantitative feedback exploring app usability, acceptability, and implementation. Feasibility of delivering a full-scale RCT will be evaluated using a priori criteria relating to app engagement, study retention and completion of candidate primary outcome measures.

**Conclusions:**

Digital screening could increase appropriate referral to perinatal mental health care. However, prior to roll out in NHS services, evidence of efficacy and cost-effectiveness is needed. The current study protocol will determine whether a full-scale RCT examining efficacy and cost-effectiveness is feasible and will inform the design of such a trial.

**Trial registration:**

Prospective ISRCTN registration (03/07/23): ISRCTN10781027; 
https://www.isrctn.com/ISRCTN10781027
.

**Supplementary Information:**

The online version contains supplementary material available at 10.1186/s40814-025-01631-7.

## Background

Perinatal mental health is a global mental health concern [1], with 1 in 5 women experiencing a change in their mental health during their pregnancy or within a year of giving birth [2]. Meta-analyses indicate that 17% of mothers develop postnatal depression (PND) during the year after their child’s birth [3, 4], with suicide the leading cause of direct maternal death from 6 weeks to 12 months postpartum [5]. Although diagnostically identical to depression at other times, the consequences and costs of PND are substantially greater due to adverse effects on infants as well as parents. PND can affect parental wellbeing, the parent-infant bond, the child’s development, and parents’ and children’s long-term physical and mental health [6, 7].

In England, the publicly funded health service (National Health Service; NHS) has identified increasing access to high quality perinatal mental health care as a key priority in its Long Term Plan [8]. For parents and their children, the lifelong consequences of not accessing such care are estimated to cost the NHS and social care £1.2 billion per 1-year birth cohort [9]. Although medication and talking therapy can be used to successfully treat PND, identifying who needs treatment is difficult. National reports [7, 9, 10] and our local audit data (unpublished) suggest that more than half of cases of PND currently go undetected and untreated. Our study seeks to improve detection of maternal PND, to allow appropriate referral to existing perinatal mental health services.

At present, there is no nationally implemented method for monitoring maternal mental health, although the Edinburgh Postnatal Depression Scale (EPDS) is widely used and has been recommended [11]. The EPDS is a 10-item screening measure, usually used in-person by health visitors, which detects PND with 81% sensitivity and 88% specificity [12]. The current UK National Institute for Health and Care Excellence (NICE) guidelines [11] recommend that health professionals consider using two initial screening questions (known as the Whooley questions) at each postnatal visit and, if symptoms are detected, consider administering the full EPDS. However, there are significant barriers to screening, including limited staff time during busy postnatal visits, lack of staff training around perinatal mental health, parental unwillingness to disclose difficulties during visits, and language barriers (e.g. 20% of Manchester adults have a main language other than English [13]). Given that more than half of cases of PND are missed [7, 9, 10], a practical, cost-effective solution is needed to improve PND detection, identify PND earlier, and enable earlier intervention.

Most (97%) people of childbearing age own a smartphone [14, 15], presenting a clear opportunity for a major advance in improving PND detection. We developed the CareLoop PND digital screening system [16], in which a smartphone app prompts parents to answer the ten EPDS questions daily and wirelessly uploads their real-time responses to a secure server. In our proof-of-concept study [16], we asked 15 mothers and 8 partners to use the app from ≥ 36 weeks pregnancy until 6 weeks postpartum. The 23 participants completed 67% of daily app-based assessments during the 6- to 12-week study period. Three mothers (20%) screened positive for PND during the study. Concurrent validity between daily app-reported and standard weekly paper EPDS was high. Mean follow-up questionnaire ratings (4.1 out of 5) suggested moderate to high app acceptability. In qualitative interviews, participants reported that the app helped them to understand their mood and to voice concerns more openly than an in-person assessment did. All participants found the app quick and easy to use; some gave suggestions to improve app engagement. Overall, the concept of digital screening was highly acceptable. This is consistent with findings from the wider digital health literature that people with common [17] and severe [18] mental health problems find smartphone apps acceptable for monitoring symptoms, alongside face-to-face care, and that digital tools may reduce stigma [19–22], aid understanding of mental health fluctuations [23–25], and facilitate help-seeking [26] in such groups.

The CareLoop PND digital screening system could transform existing screening and increase referral to perinatal mental health care, supporting the NHS Long Term Plan ambitions. However, prior to roll-out in the NHS, a full-scale Randomised Controlled Trial (RCT) is needed to determine whether adding digital screening to usual care is efficacious and cost-effective [27]. The current protocol describes a randomised feasibility trial which gathers information required to plan and deliver a future full-scale RCT evaluating the CareLoop PND digital screening system.

## Objectives

The primary objective of this feasibility trial is to examine the feasibility of delivering a full-scale, single-blind, RCT, within NHS services, comparing digital PND screening and standard practice. Feasibility will be assessed against three a priori criteria defining acceptable levels of (i) app engagement, (ii) retention, and (iii) data completeness. Secondary objectives are to examine participant recruitment, barriers to recruitment, the suitability of two candidate primary outcomes for a full-scale trial, the suitability of other proposed clinical and health economic measures, and the acceptability, usability and safety of the digital screening system.

## Methods

### Trial design

A single blind, randomised feasibility trial (usual care plus digital screening vs. usual care alone; total *n* = 80), with measures administered pre-randomisation, post-intervention (8 weeks postpartum) and at later follow-up (6 months postpartum). See Fig. 1 for a flow diagram outlining the trial design.

**Fig. 1 Fig1:**
[figure not shown]
Study design and assessment schedule. PHQ-9 = Patient Health Questionnaire; GAD-7 = Generalised Anxiety Disorder questionnaire; EPDS = Edinburgh Postnatal Depression Scale; MINI = Mini International Neuropsychiatric Interview; PBQ = Postpartum Bonding Questionnaire; HRUQ = Healthcare Resource Use Questionnaire; Abridged MARS = Mobile App Rating Scale

### Ethical approval

This study was approved by Greater Manchester West Research Ethics Committee (approval number 23/NW/0064) and the UK Health Research Authority.

### Setting

The study sponsor is Greater Manchester Mental Health NHS Foundation Trust. The multi-site study will take place across two NHS sites: Manchester University NHS Foundation Trust (MFT) and Mersey and West Lancashire Teaching Hospitals NHS Trust (MWL; formerly named St Helens and Knowsley Teaching Hospitals NHS Trust).

### Participants

#### Sample size

The study aims to recruit 80 participants. A conventional power calculation is not necessary since evaluating intervention effectiveness is not the aim of this feasibility trial. The proposed sample size is sufficient to assess feasibility outcomes (e.g. to estimate the attrition rate to within ± 11%) and to estimate key parameters (e.g. the standard deviation of candidate primary outcomes) to help inform a power calculation for the larger trial [28]. With reference to the latter, as long as an upper, one-sided 80% confidence limit is used for the estimate of the standard deviation (rather than the estimated value itself), the larger trial has an 80% chance of achieving its planned power [29].

#### Eligibility criteria

Inclusion criteria.

Less than or equal to 36 weeks pregnant; under care of Manchester Foundation Trust (MFT) or Mersey and West Lancashire Teaching Hospitals NHS Trust (MWL); aged ≥ 18 years; sufficient English fluency to complete baseline assessment (or partner speaks English fluently).

Exclusion criteria.

Fetal abnormality; major depression (Patient Health Questionnaire- 9 (PHQ-9) score ≥ 10) [30], generalised anxiety disorder (Generalised Anxiety Disorder questionnaire- 7 (GAD-7) score ≥ 10) [31] or perinatal psychosis at study entry; stillbirth, pre-eclampsia or another medical emergency requiring hospital admission (participants experiencing these conditions in relation to childbirth during the study will be withdrawn); under the care of MFT but living outside the Central Manchester area; under the care of MWL but living outside the St Helens area.

Three of these eligibility criteria require further explanation.Inclusion from 36 weeks’ gestation. Although the specific period of interest for PND screening is *after* childbirth, participants will be recruited when still pregnant (≥ 36 weeks). This is to allow time for participants to complete key study procedures *before* giving birth, rather than in the immediate postnatal period when their focus will be on caring for their baby and recovering from childbirth. Including participants only after 36 weeks’ gestation is appropriate as the likelihood of unanticipated neonatal complications is considerably lower from this point onwards.Exclusion of stillbirth, pre-eclampsia or other medical emergencies requiring hospital admission. This exclusion criterion is designed to prioritise the mental and physical health of participants during the study. Senior clinical experts on our study team considered it inappropriate for participants experiencing these distressing, life-threatening, and/or life-changing conditions to continue participating in the study. For example, requiring a parent who has just experienced stillbirth to continue to participate in a study investigating their postnatal experience is likely to add to their distress. Given that participants will be randomised during late pregnancy and that the named conditions do not typically present until childbirth itself, it is necessary to allow participants to be excluded post-randomisation if these conditions arise.Exclusion of participants outside Central Manchester and St. Helens areas. These geographical restrictions are in place to enable the research team to access relevant electronic health records (GP and health visitor records), which are only readily accessible for people living in the Central Manchester (for MFT) or St Helens (for MWL) areas. Researchers will need to access these health records to extract specific data (true/false positive PND screens via usual care screening) that underpins one of the candidate primary outcomes for a full-scale study.

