### Intervention and control groups

#### Usual care plus digital screening

Participants in the digital screening group will be asked to use the CareLoop PND app from study entry until 8 weeks postpartum, in addition to their usual NHS care. This specific intervention end date was selected to enable a fair comparison with usual care: within UK health services, at 6–8 weeks postpartum, mothers should be offered a health check, including mental health screening questions [32]. Research midwives will instruct participants in how to download, configure and use the app, with the help of an instructional video. Participants without a suitable smartphone will be lent a study phone until 8 weeks postpartum. All participants will be offered £10 phone credit per month that they are using the app, up to £30 in total.

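### The listed gestation criterion (36 weeks or less) is the reverse of the rule that the protocol's own rationale and app-use period require (36 weeks or more)

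*Protocol article*

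**What the plan says.** All statements are in the protocol article.

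- **Eligibility criteria, inclusion list:** "Less than or equal to 36 weeks pregnant". No lower limit on gestation is given.
- **Eligibility criteria, explanatory text on the same criterion:** it is headed "Inclusion from 36 weeks’ gestation". It says that "participants will be recruited when still pregnant (≥ 36 weeks"), and it gives a reason for the lower bound: "Including participants only after 36 weeks’ gestation is appropriate as the likelihood of unanticipated neonatal complications is considerably lower from this point onwards".
- **Abstract, Methods:** women in the experimental arm "will use the CareLoop PND app daily from ≥ 36 weeks’ pregnancy until 8 weeks postpartum". Recruitment is placed in late pregnancy.
- **Usual care plus digital screening:** women in this arm are "asked to use the CareLoop PND app from study entry until 8 weeks postpartum". Phone credit is £10 a month, capped at £30.

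**The concern.** The inclusion list is the rule that a screener, an auditor or a replicating team applies, and here it points the opposite way from its own justification. The direction is written in words, so it is not a symbol lost in PDF conversion.

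Several planned quantities depend on gestation at entry:

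- **App engagement**, a primary feasibility criterion, is calculated over a period that starts at entry.
- **Candidate primary outcome (a)** counts positive screens from baseline to 8 weeks after birth, so its window lengthens with earlier entry.
- **Recruitment**, the first secondary objective, uses eligible women as its denominator, and the CONSORT diagram reports reasons for ineligibility.
- **Safety calls** in the app arm are timed at 1, 2, 4 and 8 weeks after randomisation.

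If the listed rule were applied, women past 36 weeks would be turned away. Women enrolled well before 36 weeks would contribute mostly antenatal app data to a trial whose stated interest is the period after childbirth.

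**Working it through.** **1. Compare the rules.**

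| Place | Gestation at entry |
|---|---|
| Inclusion list | 36 weeks or less |
| Explanatory text, heading and recruitment statement | 36 weeks or more |
| Explanatory text, reason for the bound | only after 36 weeks |
| Abstract (app start) combined with the intervention section (app start = study entry) | 36 weeks or more |

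The list overlaps with the second and fourth rows only at 36 weeks, and with the third row not at all. A woman at 37 weeks is ineligible by the list and eligible by every other statement. A woman at 28 weeks is the reverse.

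**2. The protocol's own sample-size figure.** The article says that 80 participants estimate attrition to within ± 11%. Taking the worst case p = 0.5 and a two-sided 95% interval (both assumed): 1.96 × √(0.5 × 0.5 / 80) = 0.1096, or ± 11%. The figure reproduces and does not involve gestation.

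**3. Length of app use.** Weeks of use = (birth week − entry week) + 8. The antenatal share is (birth week − entry week) divided by that total. Birth at 40 to 42 weeks is an assumption, as the article gives no figure.

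| Entry week | Birth at 40: weeks (antenatal share) | Birth at 42: weeks (antenatal share) |
|---|---|---|
| 20 | 28 (20/28 = 71%) | 30 (22/30 = 73%) |
| 28 | 20 (12/20 = 60%) | 22 (14/22 = 64%) |
| 34 | 14 (6/14 = 43%) | 16 (8/16 = 50%) |
| 36 | 12 (4/12 = 33%) | 14 (6/14 = 43%) |
| 38 | 10 (2/10 = 20%) | 12 (4/12 = 33%) |
| 40 | 8 (0/8 = 0%) | 10 (2/10 = 20%) |

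Entry at 36 weeks or later therefore gives about 8 to 14 weeks of use. Under the listed rule there is no upper limit short of the length of pregnancy.

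**4. Indirect check against the phone credit.** £30 at £10 a month covers 3 months. At 365.25/84 = 4.35 weeks a month, that is 13 weeks. Entry at 36 weeks gives 12 to 14 weeks, or 2.8 to 3.2 months, which fits. Entry at 28 weeks gives 4.6 to 5.1 months and entry at 20 weeks gives 6.4 to 6.9 months, well beyond the cap. A cap does not prove the intended duration, but it agrees with the later-entry rule.

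**5. Safety calls.** Treating randomisation as entry, the last call falls at entry week + 8. It precedes birth if entry is before 32 weeks (birth at 40) or before 34 weeks (birth at 42). Any woman admitted earlier than that would have all four calls before birth, although the article says that the calls should roughly mirror antenatal and postnatal appointments.

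**The case against.** The strongest reply is that this is a wording slip in one line. The explanatory text that follows the list, the Abstract and the proof-of-concept study described in the Background all use 36 weeks or later, so a reader can recover the intended rule. The article condenses a fuller protocol, and nothing in it shows that sites screened to the listed line. No wrong enrolment has been demonstrated. This stands, and it makes the harm to conduct conditional.

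The size of the effect also depends on the entry week chosen. Entry at 20 weeks appears nowhere in the article and conflicts with its references to late pregnancy. At 35 weeks, with birth at 40, the antenatal share is 5/13 = 38% against 4/12 = 33% at 36 weeks, a small difference. This stands too: the 20-week figures show what the list permits, not what is likely.

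The point about calls is partly true of the intended design. With entry at 36 weeks and birth at 40, the calls fall at 37, 38, 40 and 44 weeks from the start of pregnancy, so only the last is clearly postnatal. The calls are for adverse events and technical problems, not outcome assessment. The MINI and retention assessments are fixed relative to birth, so the gestation rule does not move their dates. This limits the consequences to app engagement, the record-review window, the eligibility count and, for early entrants, the timing of the calls.

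None of this removes the contradiction. That the intended rule can be inferred from the next paragraph does not make the listed criterion correct.

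**Conclusion.** The concern holds. The listed criterion is the reverse of its own rationale and disagrees with the Abstract and the intervention period. Taken literally, it excludes women at 37 weeks or later and admits all earlier gestations.

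The effect on app exposure runs from trivial (entry at 35 weeks) to more than a doubling (28 weeks for entry at 20 weeks against 12 for entry at 36, birth at 40). These figures assume birth at 40 to 42 weeks and app use from entry to 8 weeks after birth. The sample size, the ± 11% precision and the timing of the follow-up assessments do not change. Whether any woman was screened under the wrong rule cannot be told from the article.

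The correction is necessary because the error reverses who is eligible, whatever happened in practice.

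**What to change.** 1. Reconcile the inclusion line with the explanatory text and the Abstract, so that the listed rule is the one that the protocol's rationale supports: gestation of 36 weeks or more at enrolment.
2. Settle the boundary at the same time. The explanatory text uses both 36 weeks or more and only after 36 weeks. State one, and say whether it refers to completed weeks.
3. Check that the approved protocol, the screening log and the e-CRF carry the same rule. The article defines a deviation against the approved protocol, and deviation counts feed the power calculation for the larger trial. If the approved document also has the reversed line, correct it there, so that enrolments after 36 weeks are not counted as deviations by accident.
4. List anyone enrolled outside the reconciled rule and report them with the protocol deviations.

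The cost is a one-line correction to the article and a check of the screening forms. No sample-size or analysis change is needed.

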#### Recruitment

Participants will be recruited from maternity services at the two study sites. Health professionals (e.g. obstetricians, midwives, health visitors) will identify potential participants and provide them with initial study information. When potential participants are interested, the health professional will obtain verbal or written consent to pass on their contact details to a researcher, who will provide full study information prior to collecting formal consent. The study will also be publicised via social media (e.g. Twitter (X), Facebook posts) and posters in NHS services. Posters and social media adverts will include a QR code that will lead participants to a short video advertisement of the study. Participants can self-refer by contacting the research team directly.

#### Informed consent

A researcher will provide potential participants with a verbal explanation of the study, a participant information sheet, and a weblink to view a participant information video. They will answer any questions and provide further information as required to ensure fully informed consent. Individuals choosing to participate will be asked to provide formal audio-recorded consent. Eligible individuals declining to participate will be asked for brief reasons (optional). Participants ineligible due to existing anxiety/depression will be referred to their GP, midwife, or health visitor.

### Assignment of interventions

#### Allocation and sequence generation

Following baseline assessment (see “Data collection and management” section for assessment details), participants will be randomly allocated (1:1) using an online service (www.sealedenvelope.com) to one of two study groups: usual care plus digital screening, or usual care alone. Random allocation sequences in blocks of size 4 or 6 will be generated, with separate sequences generated for each study site (MFT, MWL) to maintain balanced treatment allocation. Block sizes occur with equal frequency and are randomly determined.

